#### Secondary employer measures at 4 months

Participants will also be asked what actions they carried out to support the return of their worker. The measure for supervisors to support return to work (SSRW) [39, 40] will be adapted for this purpose.

#### Process evaluation analysis

A detailed process evaluation informed by the Implementation Outcome Framework (IOF) [41, 42] will be conducted. This framework includes eight implementation outcomes (acceptability, adoption, appropriateness, feasibility, fidelity, implementation cost, coverage and sustainability). In addition, the Theoretical Domains Framework (TDF) [43, 44], a widely used framework in behaviour change and implementation research, will also inform the process outcome data collection. Use of the TDF allows an in-depth exploration of the barriers and facilitators of implementing the trial. The data collection methods and its process outcomes outlined below capture the process outcome information for the IOF and TDF.

End of study semi-structured interview schedules will be developed to explore overall participant’s experiences using PROWORK during their sickness absence and RTW. Similar interview schedules will be created to explore the main barriers and facilitators to engaging and implementing PROWORK at the organisational level. These will be supplemented with researcher notes, including thoughts and observations about the organisation’s procedures and implementation approach and notes from the monthly calls between the research team and the organisation’s HR contact. Collectively, these will provide information on the acceptability of the trial procedures including randomisation, the measurement instruments and the overall acceptability of the intervention. Interviews and monthly calls will be conducted by a conferencing platform, so they can be recorded and transcribed verbatim. Short employer interviews (e.g. with HR, health and safety manager) with intervention and control sites at monthly intervals will be conducted to explore any changes to policies or processes that may impact the study. Questions around study participation (e.g. identifying workers on sick leave, sending out study information) will also be explored, and formal notes will be taken as part of the process evaluation. A detailed plan of the measures and methodologies used in the process evaluation is described below.

### Process outcomes

The number of organisations agreeing to participate in the trial will be summarised in terms of their size, sector, sick leave and RTW polices and number of workers who were on long-term sick leave in the past 12 months prior to the start of the study.The number of worker participants identified on long-term sick leave and the number recruited into the study will be reported, along with the number of participants followed up at each timepoint. Withdrawals (and where possible, reasons for withdrawals) will be reported.Difference in recruitment uptake rate and follow-up rates at each time point will be compared between the intervention and control arms.As organisations of different sizes are taking part, it is likely there will be some imbalance between participants in each treatment arms on one or more baseline characteristics. Baseline comparisons will be carried out to detect any substantial differences between participants recruited from the control and intervention arms. This will be done by scrutinising the baseline data for any serious imbalances in observable baseline variables and the trends of the imbalance if any. The recruitment rates will also be estimated and compared between the control and intervention arms. The size of any imbalances will be examined, in addition to evidence of systematic selection bias in the types of patients being recruited in control versus intervention armsKey baseline characteristic will be compared between those participants followed up and those lost to follow-up at each timepoint.Intervention fidelity will be assessed by the log in and downloads of the toolkits. Successful adherence is defined as at least 60% download of the total toolkit by workers and employers (i.e. those with a responsibility for managing RTW) and at least 60% completion of the activities/checklist in total.Following the guidance from the COREQ-32 checklist [45], qualitative interview data for the process evaluation will be recorded, transcribed verbatim and coded following the principles of thematic analysis [46].The Theoretical Domains Framework [43], and the normalisation process theory [47], will be used to guide thematic analysis of the qualitative data. The findings will be supplemented with observations made by the researchers throughout the implementation of the intervention. Collectively, these will provide information on the acceptability of the trial measurements and the intervention.Survey data for the process evaluation will be summarised using means, standard deviations, medians and ranges for continuous variables and counts and percentages for categorical variables.The pilot data will provide information on the parameters needed for a realistic sample size calculation (mean and standard deviation) for a future, main cluster RCT.

#### Participant appreciation

As a thank you for participating in the pilot trial, participants will have the chance to win a £50 gift voucher for every survey they complete during the baseline and follow-up measures to encourage participation.

#### Cost analysis

The cost analysis will be exploratory, with the aim to inform the design of a full cost-utility analysis alongside a future main trial. Data on costs will be sought from all participants, and results will be presented taking into account worker-incurred costs and productivity losses. Analyses will be mainly descriptive, and all costs and outcomes will be summarised using means and 95% confidence intervals.Healthcare resource used will be collected using self-completed questionnaires at baseline, 2 and 4 months, with a recall period of 2 months in each. Questions will ask workers to recall GP consultations, visits to healthcare professionals, outpatient appointments, investigations or treatments and inpatient stays related to the index condition (adapted from Peveler et al., 2005 [38]). Participants will be asked to distinguish between National Health Service (NHS) and private practice visits.Resource used for the intervention will be directly recorded and costs attached, staff time (e.g. coaching sessions, training sessions), materials (posters, flyers, referral forms, website set-up and maintenance, toolkit printing) and training sessions.Costs will take into account both absenteeism and presenteeism and will utilise self-report data on employment status, occupation and time off work and reduced productivity at work (presenteeism).All workers will be asked to complete the 5-level version of the EuroQoL-5DL (EQ-5DL) (1990) [48] (questionnaire at baseline, 2 months and 4 months) in order for the quality-adjusted life years (QALYs) over the 6-month time period to be calculated for each participant. The QALYs combine information on health-related quality of life and survival.Productivity costs will be calculated using data collected on the absence from the number of days taken to RTW.Using the human-capital approach (which assumes that the value of lost work is equal to the amount of resources an individual would have been paid to do that work), the self-reported days of absence will be multiplied by the respondent-specific wage rate.

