## Methods/design

### Study design

This is a feasibility randomised controlled trial with a 4-month intervention (called PROWORK) to be delivered to employees and managers in SMEs and LEs. Each of the organisations are the units of randomisation (the clusters), with data collected from individual workers (the participants). In addition, managers with a worker on LTSA will be eligible to participate. Although dyads of managers and workers can participate, this is not essential. This design overcomes the problem of contamination between the intervention and control arms and the problems associated with individually consenting and randomising workers to a trial where the employers may be managing the sick leave of 2 or more workers. A repeated measures design will be adopted, whereby worker participants will complete outcome measures at baseline, 2 months and 4 months, and managers will complete outcome measures at baseline and 4 months. Each organisation’s involvement in the trial is for 12 months. Observations and end-of-study interviews with workers and managers and informal monthly meetings with the organisation’s human resources representative will be conducted throughout the intervention period as part of a full process evaluation. Figure 1 shows the study flow diagram, and Table 1 indicates the schedule of enrolment, intervention and outcome measures. The project has been granted ethical approval by the Loughborough University Ethical Advisory Committee (reference 2020-1889-2041). The trial was preregistered in the ISRCTN registry on 15th December 2020 (10.1186/ISRCTN90032009).

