#### Outcome measures

Primary and secondary outcome measures will be collected at baseline, 2 months and 4 months. Outcome measures will be collected for both workers and managers. Outcome measures have been grouped as process outcomes and research outcome measures (see below), and they will be collected using Qualtrics; data and personal details will be stored according to the General Data Protection Regulation (GDPR, 2016/679) and research governance guidelines. A summary of the outcome measures at the various time points is provided in Table 3. Qualitative interview data will be collected either over the phone or using online conferencing facilities. Both full-return (defined for this study as working the same days or hours per week as before sickness absence in an identical or equivalent role for at least 4 weeks) and partial RTW (defined as working any number of hours in any role) data will be collected via text messages.

**Table 3 Tab3:** Schedule of process and research outcome measures

Measured outcome	Assessment tool	Pre-randomisation	Baseline	Month 1	Month 2	Month 3	Month 4
Process outcomes							
Long-term sickness absence data for the past 12 months	Reports review	**X**					
Frameworks (sickness absence policy, return-to-work policy, mental health training and support)	Policy review	**X**					
Number of workers on (a) sick leave (≥ 8 days) and their reasons and (b) that employers have contacted to take part in the study (until the end of the study)	Checklist		**X**	**X**	**X**	**X**	**X**
Number of persons responsible for managing the sick leave and return to work (a) consenting to take part and (b) attending the training	Checklist	**X**					
Toolkit use	Volute records and interview		**X**				**X**
Feasibility and acceptability of intervention	Interview						**X**
Toolkit use	Interview						**X**
Research outcome worker							
Workers sick leave	Self-reported number of days						**x**
Depression	Patient Health Questionnaire- 9		**X**		**X**		**X**
Anxiety	General Anxiety Disorder-7		**X**		**X**		**X**
Sick leave duration	Number of days on sick leave		**X**		**X**		**X**
Self-efficacy to RTW	11-item Return-to-work Self-Efficacy Scale		**X**		**X**		**X**
Readiness to RTW	13-item Readiness to Return to work		**X**		**X**		**X**
Readiness to stay at work	9-item Readiness to Stay at Work Scale		**X**		**X**		**X**
Workplace communication	6-item Workplace Health Communication Scale		**X**		**X**		**X**

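### QALYs are to be calculated over 6 months, but EQ-5D, healthcare use and return-to-work data all stop at 4 months

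*Protocol article*

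**What the plan says.** The Cost analysis section has workers complete the EQ-5D ("questionnaire at baseline, 2 months and 4 months") so as to allow "quality-adjusted life years (QALYs) over the 6-month time period to be calculated for each participant". The same section sets the cost data: "Healthcare resource used will be collected using self-completed questionnaires at baseline, 2 and 4 months, with a recall period of 2 months in each".

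The rest of the article is consistent about when worker follow-up ends:

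- Study design: "worker participants will complete outcome measures at baseline, 2 months and 4 months".
- Table 1 (SPIRIT schedule): quality of life and healthcare use at baseline, 2 months and 4 months only. The economic evaluation and the intervention resource rows are also marked at end of study, but neither of these two worker questionnaires is.
- Table 3: the EuroQol measure at baseline, month 2 and month 4 only.
- Workers: the last follow-up is 4 months after the worker completes the baseline measures.
- Primary worker measures: the last sick-leave and return-to-work data are collected 4 months after randomisation.

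No section gives participants a 6-month assessment or a rule for extending utilities beyond month 4. The only other 6-month study period is the window for recruiting organisations (Sample size), which is unrelated.

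**The concern.** A QALY is utility accumulated over time, so its horizon is part of its definition. Three measurements spanning 4 months cannot give a 6-month QALY without an assumption about months 5 and 6, and the plan states none. Two analysts following the text could report different QALYs from the same data.

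The second problem is alignment. Healthcare use after baseline is known for 4 months. Setting 6-month QALYs beside 4-month costs would credit health gains over a period whose costs were not counted. One stated purpose of this analysis is to inform a full cost-utility analysis alongside a later main trial, so a mismatched horizon could be carried into that design.

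**Working it through.** **1. Can the 6 months be reproduced?** Inputs: EQ-5D at t = 0, 2 and 4 months (Cost analysis, Tables 1 and 3).

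- Span observed: 4 − 0 = 4 months. The stated 6 is not reproduced.
- Uncovered share: (6 − 4)/6 = 33.3%.

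**2. Could 6 months mean the total recall period of the resource-use questionnaires?** With 2 months of recall at each of 0, 2 and 4 months, the windows are −2 to 0, 0 to 2, and 2 to 4. They add up to 6 months, but the first lies before baseline, where there is no EQ-5D. Only 4 months after baseline are costed, and 2 of the 6 months still lack utilities. This reading does not rescue the figure.

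**3. Size of the horizon difference.** At full health throughout, the QALY is 4/12 = 0.333 over 4 months and 6/12 = 0.500 over 6.

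**4. Dependence of an individual's QALY on the extrapolation.** Area under the curve: sum of (t[i+1] − t[i])/12 × (u[i] + u[i+1])/2. Utilities of 0.50, 0.60 and 0.70 are assumed for illustration.

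- 4 months, observed: (2/12 × 0.55) + (2/12 × 0.65) = 0.200
- 6 months, last value carried forward: 0.200 + 0.70 × 2/12 = 0.317
- 6 months, linear trend continued to 0.80: 0.200 + 0.75 × 2/12 = 0.325
- 6 months, scaled by 6/4: 0.300

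**5. Dependence of a between-arm difference.** Differences at 0, 2 and 4 months are assumed. The 6-month value either carries the month-4 difference forward or lets it fade linearly to zero at month 6.

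| Assumed difference at 0, 2, 4 months | Observed, 4 months | 6 months, fading | 6 months, carried forward | Share extrapolated |
|---|---|---|---|---|
| 0, 0.05, 0.10 | 0.0167 | 0.0250 | 0.0333 | 33% to 50% |
| 0, 0.05, 0.05 | 0.0125 | 0.0167 | 0.0208 | 25% to 40% |
| 0, 0.05, 0 | 0.0083 | 0.0083 | 0.0083 | 0% |

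First row: the observed part is 2/12 × 0.025 + 2/12 × 0.075 = 0.0167. Carrying forward adds 0.10 × 2/12 = 0.0167, so the share is 0.0167/0.0333 = 50%. Fading adds 0.05 × 2/12 = 0.0083, so the share is 0.0083/0.0250 = 33%. The extrapolated share depends on the pattern assumed, and one half is the top of the range shown.

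**The case against.** The strongest reply is that this is a slip of one digit. Every schedule ends at 4 months and nothing in the article plans an extrapolation, so the analysts would probably compute 4-month QALYs in any case. The cost analysis is also described as exploratory and mainly descriptive, reported as means with 95% confidence intervals. The section specifies neither an incremental QALY nor a cost-effectiveness ratio, and it places the full cost-utility analysis alongside a future trial. All of this stands and limits the consequence. It does not make the sentence right: the figure is a stated analysis rule that contradicts the measurement times given in the same sentence. Nor is this a detail that a condensed article leaves to a fuller document.

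A reader might also infer a second error, in the productivity costs. The section says "Productivity costs will be calculated using data collected on the absence from the number of days taken to RTW", and Outcome measures has "partial RTW (defined as working any number of hours in any role". Together these could suggest that hours lost after a partial return are costed as nothing. The documents do not support that. The same Cost analysis section says that costs cover both absenteeism and presenteeism, drawing on self-reported time off work and reduced productivity. The secondary worker measures include the WPAI:GH at 2 and 4 months for those who have returned. Partial and full returns are recorded separately, and the section does not say which of the two ends the absence count. Costing the difference between usual and current hours would also need the worker's hours before sick leave. The listed questions ask only for current hours and whether they are the same as before.

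**Conclusion.** The 6-month QALY horizon is wrong as written. One third of it has no utility data, no extrapolation rule is stated, and it does not match the 4-month post-baseline cost window. These statements follow from the article's own schedule and need no assumption.

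The effect on a between-arm QALY difference can only be illustrated. With a difference growing linearly to month 4, one third to one half of a 6-month gain would be extrapolated. The share is smaller if the difference levels off and nil if it has gone by month 4. It would be too strong to say that half of any reported gain is extrapolated, or that the sponsor intends to carry values forward, since the article says neither. The point should be corrected, but it concerns an exploratory analysis and does not touch the feasibility outcomes.

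**What to change.** In Cost analysis, replace the 6-month period with the 4-month follow-up, and say that QALYs are the area under the curve from the EQ-5D at baseline, 2 and 4 months. Add that costs are presented over the same 4 months after baseline, with the 2 months recalled at baseline reported separately as pre-baseline use.

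This changes one figure and adds a short clause. It needs no new data and leaves the schedule as it is. If a 6-month horizon is really intended, the plan would need either a 6-month EQ-5D and resource-use assessment or a stated extrapolation rule applied to both QALYs and costs. Either would cost more than aligning the text with the data already planned.

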### Statistical data analysis

This study will be analysed according to the Consolidation Standards of Reporting Trials (CONSORT) statement for cluster RCTs [49]. As this is a feasibility study, main analysis will include descriptive statistics (mean, SDs and medians). Data will be analysed using IBM SPSS statistics. Data analysis will be performed after the last trial participant has completed their 4-month post-intervention. A baseline table (descriptive statistics and frequencies) will compare the demographic and clinical characteristics including gender, age, education, number of days on sick leave, mental health status, readiness, intention and self-efficacy to RTW, work support, communication, performance at work, sleep and physical activity, between the 2 arms. As this is a pilot trial, no emphasis will be put on the *p*-values, as the main purpose of the analysis is to calculate confidence intervals (CI). Statistical analysis will be carried out on an intention to treat basis with missing outcome data being imputed using multiple imputation. To explore the extent and patterns of missing outcome data, we will report the proportion of missing values per item, proportion of participants who complete all items on the questionnaire and the proportion of respondents who answer at least 50% of the items in a scale. The proportion of missing data will also be reported for the other key outcomes and compared between the participants from intervention and control practices. The point estimate of the proportion and its 95% confidence interval (CI) will be provided for the primary research outcome, i.e. number of days taken to RTW (partial or full) for the intervention and the control arms. Key baseline characteristic will be compared between those participants followed up and those lost to follow-up at each timepoint.

#### Data management and research governance

All data will be anonymised and entered into a secure database and only accessible by trial staff and authorised personnel. The study will comply with the Data Protection Act which requires data to be anonymised as soon as it is practical to do so. Personal data will be processed on the public task basis under the General Data Protection Regulation (GDPR). The study will be sponsored by Loughborough University. An independent Trial Steering Committee (TSC) will be created to oversee the evolution of the study, and they will meet every 4 months. Due to the low-risk nature of this study, no adverse events are anticipated to occur; however, should any arise, the TSC and the Loughborough University guidelines will be consulted for the managing and reporting of any intervention-related adverse events.

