#### Allocation to intervention

In this pilot RCT, organisations will be stratified by size. To avoid study contamination, organisations will be randomised into the intervention or active control group after baseline measures are taken using an allocation ratio of 1:1. Randomisation will be carried out by computer-generated randomisation stratified by organisational size (small, medium or large).

Consented workers will be allocated to either the intervention or active control group based on the randomisation of their participating organisation. Baseline data will be collected from each participant prior to either being given the RTW toolkit (intervention group participant) or supporting information (active control group participant). The participating workers and employers will not be blinded in group allocation.

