### Workers

Workers on sick leave will receive the intervention until RTW or 4 months (last follow-up) from when the worker has completed baseline measures. PROWORK includes a step-by-step action-oriented toolkit that provides guidance and support from initial absence to post RTW. Three workplace coaching sessions based on goal setting and problem-solving will be offered to worker by a trained project researcher over the phone. These will be delivered at three timepoints throughout the intervention: (1) at the start, to support making contact, to coach the participant in the use of the resources, to build a relationship with the participant and to direct the participant to external resources available in the toolkit; (2) at 2 months to coach them for preparation to RTW, or if they have returned to work, and then to coach them in adjusting back to work; and (3) at 3 months to either coach them for preparation to RTW or if they have returned to work and then to coach them in adjusting back to work. The coaching sessions aim to motivate and support workers to use the RTW toolkit, to help them with any activities they might feel stuck with and to discuss their action plan to avoid any relapse. During these sessions, and as part of the process evaluation, the workplace coach will ask about what resources are the worker finding more useful and what are the benefits of using this toolkit.

To reinforce the message of having regular communication with the workplace whilst on sick leave, the worker will have the option to contact the workplace coach (i.e. project researcher) when needed either by email or phone call.

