#### Active control group

To compare the effects of the intervention against usual practice, organisations allocated into the control group will be asked to continue with their usual procedures, and no training or guidance will be offered. Participants in the control group will be asked to complete the same measurements as those in the intervention group and at the same timepoints. At the end of the PROWORK study, organisations in the control group will receive a report evaluating their current RTW policies and procedures, access to the line manager training and hard copies of both toolkits.

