### Trial feasibility and acceptability-related outcomes

We will collect data on the following:Willingness of organisations to take part (baseline) and retention through follow-up with reach, uptake and completion as primary endpoints.Proportion of workers on sick leave referred to pilot study (> 50% green for main trial to go ahead, 30–50% amber; < 30% red).Proportion of workers and line manager participating in both control and intervention groups (worker: > 50% green, 30–50% amber; < 30% red)For intervention worker participants, short worker interviews will be conducted at each coaching session (at intervention start, 2 months and 3 months) to explore use of the toolkit.At 4 months (end of intervention), an interview will be conducted with both worker participants and line manager/RTW contacts to ask them about their engagement, usage and the effectiveness of the toolkit. Information regarding barriers and facilitators to implementation, functionality and interest in on-going usage will also be assessed.At the end of 12-month study period, organisational stakeholder will be interviewed to explore their perceived benefits of the intervention (engagement, usage, functionality and the effectiveness of the toolkit), as well as barriers/facilitators to implementation, interest in on-going usage and whether the intervention could form part of any workplace RTW policies.Costs associated with toolkit website build and delivery, training delivery, coaching sessions and other associated costs will be collected.

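### Adverse events are handled passively and only if intervention-related, so adverse-event counts cannot be compared between arms

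*Protocol article*

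**What the plan says.** The only adverse-event provision is in *Data management and research governance*. Citing the study's low risk, it states that "no adverse events are anticipated to occur; however, should any arise", the Trial Steering Committee (TSC) and the university's guidelines will be consulted "for the managing and reporting of any intervention-related adverse events". Neither Table 1 nor Table 3 lists an adverse-event item.

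Contact with workers differs by arm. Under *Workers*, "Three workplace coaching sessions based on goal setting and problem-solving will be offered to worker by a trained project researcher over the phone", at the start, 2 months and 3 months, and "the worker will have the option to contact the workplace coach (i.e. project researcher) when needed either by email or phone call". *Trial feasibility and acceptability-related outcomes* adds: "For intervention worker participants, short worker interviews will be conducted at each coaching session". Under *Active control group*, control organisations "will be asked to continue with their usual procedures, and no training or guidance will be offered". *Allocation to intervention* states: "The participating workers and employers will not be blinded in group allocation".

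Other data are collected alike in both arms, because controls complete the same measurements at the same timepoints (*Active control group*):
- PHQ-9 and GAD-7 at baseline, 2 and 4 months (*Secondary worker measures*).
- Self-reported health-care use at the same times, including inpatient stays for the index condition (*Cost analysis*; listed in Table 1).
- Withdrawals, with reasons where possible (*Process outcomes*).
- Monthly texts to workers (*Trial research-related outcomes*) and monthly employer interviews at intervention and control sites (*Process evaluation analysis*).

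**The concern.** Two features of the stated rule act in the same direction. Causality is used as an entry filter, and the filter can pass events from one arm only. Events also come to notice only if someone mentions them, and the described occasions for a worker to mention one to the researcher lie mostly in the intervention arm.

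Eligible workers are off sick with poor mental wellbeing as cause or comorbidity, and the coaching itself covers avoiding relapse. Some deterioration is foreseeable in both arms whatever the intervention does. Without a control count gathered in the same way, the TSC cannot tell background events from events caused by the toolkit or the coaching. The feasibility study would also pass on an untested method of capturing harms to the larger trial that it is meant to inform.

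**Working it through.** The plan states no event rate or harms target, so there is no figure to reproduce. The check is mainly a comparison of the passages.

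**Step 1: the relatedness filter.** Only intervention-related events fall within the stated managing and reporting. Control workers receive usual practice. Their number of intervention-related events is therefore 0 by definition, whatever happens to them.

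**Step 2: opportunity for an event to surface.**

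| Route during follow-up | Intervention workers | Control workers |
|---|---|---|
| Scheduled coaching calls, with short interviews | 3 (first at the start, so 2 later) | none described |
| Contact with coach on demand | yes | none described |
| Monthly text on sick leave and return to work | yes | yes |
| 2- and 4-month surveys | yes | yes |
| Monthly employer interview (with the site, not the worker) | yes | yes |

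None of these routes is described as asking about adverse events. End-of-study worker interviews are also planned. The 4-month interview is described as being about the toolkit, and whether controls are included is not stated.

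**Step 3: illustration of unequal detection alone, with the relatedness filter ignored.** Expected recorded events per arm = n × p × d, where n is workers per arm, p the true risk (the same in both arms) and d the probability that an event is recorded. The *Sample size* target is 30 per arm, workers and managers together, so n = 30 is generous. The values of p and d are assumptions: d = 0.9 for intervention, and 0.5 or 0.3 for control.

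| p | Intervention, d = 0.9 | Control, d = 0.5 | Control, d = 0.3 |
|---|---|---|---|
| 5% | 30 × 0.05 × 0.9 = 1.35 | 0.75 | 0.45 |
| 10% | 30 × 0.10 × 0.9 = 2.7 | 1.5 | 0.9 |
| 20% | 30 × 0.20 × 0.9 = 5.4 | 3.0 | 1.8 |

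The apparent ratio is 0.9/0.5 = 1.8 or 0.9/0.3 = 3.0 at every risk, with no true difference. If half the 30 were managers (n = 15), the counts would halve and the ratios would stay the same. With the filter applied, the control column becomes 0.

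**Step 4: what complete capture could show.** For 0 events in 30, the exact upper limit is 1 − 0.05^(1/30) = 9.5% (one-sided 95%) or 1 − 0.025^(1/30) = 11.6% (two-sided 95%). These limits treat workers as independent. Clustering within organisations, or fewer than 30 workers, would generally weaken the evidence further.

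**The case against.** The case for leaving the text alone has real substance.

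- *Harms are already measured in both arms.* Symptom scores, index-condition inpatient stays and withdrawals are collected alike. A reader might infer from the governance paragraph that harms cannot be compared at all, and the documents do not support that. What remains is that the article does not designate these data as harms or route them to the TSC. The scores are also snapshots at three timepoints, and the admissions are limited to the index condition.
- *Controls are not out of contact.* A reader might infer that only the intervention arm has live contact. That is too broad, given the monthly employer interviews at control sites and the monthly texts to control workers. The accurate statement concerns scheduled spoken contact with workers during follow-up.
- *No decision depends on the count.* The stated traffic-light criteria concern referral and participation, and the objectives include no comparison of harms between arms. An inference that the main-trial decision would be distorted goes beyond the text.
- *The article is condensed.* It refers to university guidelines that are not shown, and it does not say that unrelated or control-arm events go unrecorded. It names no assessor of relatedness. The coach is a project researcher who would know the arm, but that this person would judge relatedness is only an inference.

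These objections narrow the point. They do not remove it, because it rests on the scope the article states and not on missing detail.

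**Conclusion.** The point holds in a limited form. As stated, adverse-event handling is passive and restricted to intervention-related events. The control count is therefore zero by definition, and any count by arm also reflects unequal opportunity to report. This applies to adverse-event counts only.

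The size cannot be derived from the documents. The 1.8-fold and 3-fold ratios rest entirely on assumed detection probabilities and show direction, not an estimate. With a target of 30 participants per arm, managers included, even a complete and symmetrical record would be descriptive: zero events would still be compatible with a risk of up to 11.6%. The point is a worthwhile, inexpensive improvement to a low-risk feasibility study, and not a flaw that undermines its feasibility aims.

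**What to change.** In *Data management and research governance*, replace the restriction to intervention-related events with a rule on recording:

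- List in advance a short set of adverse events (for example hospital admission, crisis contact, or worsening of the condition behind the absence) and record them whatever the presumed cause.
- Ask about them with one identical item in the existing 2- and 4-month worker surveys of both arms.
- Record relatedness afterwards, as a separate field.
- Tabulate counts by arm for the TSC and in the results, with the number of workers surveyed as denominator. Show events volunteered to the coach on a separate line.
- Use the existing health-care questionnaire as the source for index-condition admissions, and PHQ-9 and GAD-7 for worsening.
- State that the counts are descriptive and do not enter the progression criteria.

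The cost is one survey item, one table and review of more events, most of them unrelated. Because workers know their allocation, willingness to report may still differ by arm, but the question and its timing would be the same. The change concerns recording and reporting only.
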